**Primary Analysis Plan**

Preparation of the survival endpoint: The timing of death is recorded only with the precision of a calendar day, so adjustments are needed to develop the survival estimates. For deaths that occur on the same day of transfusion, a death indicator representing 0.5 days will be administratively assigned. For deaths out to day 7, integer counts of the number of calendar days post transfusion will be computed. For records of patients transfused but do not contain any post transfusion data, these patients will be administratively censored at day 0.25. Otherwise, the length of known vital status will be used to determine inclusion in the risk set (e.g., reported alive in the daily summary, assessed for the day 7 follow up, etc).

The primary analysis of antibody titer data will first consider a Cox proportional hazards model using a spline fit on the observed antibody concentration line. The spline is to avoid a strong linear assumption on the relationship of the titer and survival. At least three knots will be considered to allow the dose-response relationship to follow a general sigmoid shape if one is present in the data. A partial likelihood test will be constructed to test for the main effect of antibody levels in the data. Should this test be statistically significant at the alpha=0.05 level of significance (two-sided), simplifications of the model to facilitate secondary analyses will be constructed. Using partial dependence plots, the general functional form of the association of antibody concentration will be associated with the probability for mortality. Without loss of generality, we assume there will be low, moderate and high concentration groups that will be identified (i.e., the three main pieces of the hypothesized sigmoid dose-response relationship). Using these as defined strata, a log rank test will be constructed using these categories.

Secondary data analyses to assess for risk modification can follow in two ways. First variable by concentration interactions terms can be added to the Cox model. While this approach is statistically efficient, the complexity of the resulting model will make real-world interpretations of the findings challenging. To address this, a Breslow-Day stratified analysis approach will be considered.

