### Primary Data Analysis: The primary analysis will be conducted through a series of unadjusted and adjusted survival models. This is required given the study is non-randomized and factors that may affect overall survival may serve as a confounding variable in the analysis. The primary hypothesis presents three variables that are hypothesized to have an impact on mortality.

First, the time to transfusion is considered. Based on early reports with convalescent plasma, a target window of 0 days, 1-3 days was considered optimal. Therefore, patients are divided into a group representing "timely" delivery of convalescent plasma. The remaining subjects are split into two groups, Days 4-10 (i.e., a week following a timely period) and Days 11+. In some analyses to aide in the graphical presentation of the data, the timeliness data is dichotomized into <=3 days vs. 4+ days.

Second, the transfusion volume on the first day of transfusion (if more than 1 transfusion was given). For this analysis, various categorizations of the volumes were considered, however, for the primary analysis, a spilt at 225 ml was implemented. This effectively separates people that received 1 unit (~ 200ml) from those that deliberately received more than 1 unit of plasma. 225 ml was selected to all for some variance in the volume in the first unit of plasma.

For the final component of the analysis, the neutralizing antibodies are both semi-quantitative and categorical in interpretation. There are lab established thresholds for negative (<1:80) and serial dilution allows for estimates ranging from 1:80 to >=1:2560. The analysis will consider the levels of the titers as nominal values as well as introducing some thresholds to classify the titers into a "low" vs. "high" classification. The original statistical analysis plan consisted of a planned analysis of the titer data using a splined fit on the observed antibody concentration. The spline was to avoid a strong linear assumption on the relationship of the titer and survival. The decision to use that approach was changed post hoc to the dichotomized approaches to account for the lack of dose-response relationship observed with the data. This decision allowed for simplification of the data presentation.

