### Secondary Data Analysis: In the future, additional secondary data analyses to assess for risk modification can follow in two ways. First variable by concentration interactions terms can be added to the Cox model. While this approach is statistically efficient, the complexity of the resulting model will make real-world interpretations of the findings challenging. To address this, a Breslow-Day stratified analysis approach will be considered. For this initial report, separate results by strata of interest are presented. The strata presented represent important subsets of the data that warrant further consideration.

For this future analysis, estimated mortality rates will be estimated using the product limit estimator for each stratum of the data. This approach will follow a generally hierarchical process. First, as noted above, the data will be stratified by time of transfusion, infusion volume, and antibody concentration level. Next, stratification will be based on admission to ICU at time of transfusion, yes or no, which result in multiple strata of interest (e.g., ICU patients transfused within 3 days using 2 units of plasma with high concentration of neutralizing antibodies). This general approach will continue with additional risk modifiers as indicated below to result in finer and finer sub categorization of patients. These estimates will be visualized with forest plots to provide an overall impression of heterogeneity among the risk modifiers. As with the primary analysis, the data will be grouped so that the three antibody concentrations levels will be collocated on the figure to provide some evidence of the dose-response relationship, if one exists. Formal tests for the effect modification will be conducted using the Cox framework using appropriately chosen interaction terms.

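### SAP v5.0 replaced the planned titre spline with unnamed low/high splits because no dose-response was seen, and its titre tests and intervals make no allowance for that

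*Supplement*

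**What the plan says.** SAP v5.0 is the latest plan shown. Under Statistical Hypotheses, its primary hypothesis has three components: timeliness of transfusion, volume, and antibody quantity on the first transfusion day.

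Under Primary Data Analysis it recalls that the original plan "consisted of a planned analysis of the titer data using a splined fit on the observed antibody concentration". It states that this was "changed post hoc to the dichotomized approaches to account for the lack of dose-response relationship observed with the data", and adds that the change simplified presentation. The replacement treats titre levels as nominal values, alongside "introducing some thresholds to classify the titers into a 'low' vs. 'high' classification". No threshold value, number of thresholds or selection rule is given. The timeliness groups and the 225 ml volume split, by contrast, are stated. The titre scale is given: "There are lab established thresholds for negative (<1:80) and serial dilution allows for estimates ranging from 1:80 to >=1:2560".

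The same section provides 95% score intervals for crude mortality and bootstrap percentile intervals, without p-values, for adjusted relative risks. Where inference is wanted, it refers the reader to the hazard ratio and its test. None of this allows for the switch or for the choice of cut.

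Secondary Data Analysis, claiming to follow the primary analysis, says that "the three antibody concentrations levels will be collocated on the figure to provide some evidence of the dose-response relationship, if one exists".

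For context, SAP v2.0 (Primary Analysis Plan) specified the spline: "At least three knots will be considered to allow the dose-response relationship to follow a general sigmoid shape". Its condition for grouping was: "Should this test be statistically significant at the alpha=0.05 level of significance (two-sided), simplifications of the model to facilitate secondary analyses will be constructed".

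**The concern.** A change of method between versions is no fault in itself. The fault lies in the reason that v5.0 gives for its current method: the relation between titre and outcome was looked at, no gradient was seen, and the form of the analysis was then altered. A p-value or 95% interval has its stated error rate only if the comparison would have been the same whatever the data showed.

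Two features make this worse. The cut is left open, so a reader cannot tell one assay-based split from one picked among several. And v2.0 allowed grouping only after a significant spline test, whereas v5.0 groups because no dose-response was seen.

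At stake is any claim that high-titre plasma goes with lower mortality. Such a claim could come from selection alone and still be read at face value as a result on the primary hypothesis.

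**Working it through.** The documents give no power, effect size, event count or titre distribution, so there is no figure of the plan's to reproduce. The only benchmarks are the two-sided 0.05 level in SAP v2.0 and the 95% intervals in v5.0.

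**Inputs from the documents**
- Titre levels: negative (<1:80) plus six dilutions from 1:80 to >=1:2560. That is 7 ordered levels, hence 7 − 1 = 6 possible low/high splits.
- Planned smooth test: a spline with at least three knots; the type is not stated.

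**Assumptions**
- Share of patients per level, lowest to highest: (A) one seventh each; (B) 25, 20, 20, 15, 10, 6, 4%; (C) 5, 12, 20, 26, 20, 12, 5%.
- Restricted cubic spline with 3 or 4 knots (2 or 3 df).
- No titre effect. Large-sample score tests, so neither sample size nor mortality enters.

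**Step 1: a bound.** For k independent tests at 0.05, the chance of at least one false positive is 1 − 0.95^k: 5.0% for k = 1, 14.3% for k = 3 and 26.5% for k = 6.

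**Step 2: allow for correlation.** Different splits of the same titre scale are correlated. If F_a < F_b are the proportions below two cuts, the correlation of their test statistics is √[F_a(1 − F_b) / (F_b(1 − F_a))]. Under (A), the two lowest cuts give √[(1/7 × 5/7) / (2/7 × 6/7)] = √(5/12) = 0.65, and the two extreme cuts give √[(1/7 × 1/7) / (6/7 × 6/7)] = 1/6 = 0.17. The true rate for six cuts is therefore below 26.5% but well above 5%.

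**Step 3: simulation** (400,000 replicates per scenario; range over A-C and both splines):

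| Strategy, no titre effect | Chance of at least one p < 0.05 |
|---|---|
| Planned spline test alone | 4.9-5.1% |
| Spline, then one outcome-blind cut if not significant | 7.8-8.8% |
| Spline, then best of three cuts | 13.8-15.0% |
| Spline, then best of six cuts | 20.1-23.0% |
| Best of six cuts, ignoring the spline | 19.7-22.6% |

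The second row can be checked by hand. Given a non-significant spline, one fixed cut rejects 3.0-4.1% of the time. So the overall rate is 0.05 + 0.95 × 0.030 = 0.079 up to 0.05 + 0.95 × 0.041 = 0.089, which agrees up to rounding and simulation error.

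**Step 4: intervals.** If the most significant of six splits is shown, its 95% interval covers the no-effect value only 1 − 0.226 = 77% to 1 − 0.197 = 80% of the time.

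**Step 5: what would hold 5%.** The 95th percentile of the largest |Z| over six cuts is 2.54-2.59, a nominal p of about 0.010-0.011. Bonferroni would require 0.05/6 = 0.0083.

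**Cross-check.** A separate simulation with assumed N = 3,000 and 22% mortality gave 20.7% and 22.3% for the best of six cuts under two titre distributions.

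**The case against.** The strongest reply is that nothing confirmatory is claimed. Protocol v10.0 calls all efficacy and safety analyses exploratory (section 9.1) and describes the titre work as an exploratory analysis that may be done (section 8.1). SAP v5.0 states no alpha and discloses the switch and its reason. This lowers the stakes. But v5.0 still places titre in its primary hypothesis and points to significance tests, and neither label nor disclosure restores an error rate.

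Several narrower objections stand:
- A threshold effect is compatible with v5.0's hypothesis, which no longer names dose-response.
- Nominal levels are planned alongside the splits, not as a fallback, and showing every level gives some protection against a hidden cut.
- The three-level display belongs to a future analysis, although it is said to follow the primary one.
- The adjusted relative risks carry no p-values. The p-value point therefore concerns the Cox tests, and the interval point concerns the titre contrasts.
- The summary of SAP changes links low/medium/high groups to assay dilutions. It does not explain the low/high splits, which v5.0 attributes to the data.

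A reader might infer that the spline test was run and failed, and that cuts were then searched for the best p-value. The documents do not say so. They report an observed lack of dose-response, with no spline p-value, no count of cuts and no search.

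A reader might also infer that splitting necessarily costs power. That depends on the shape of the effect. With assumed N = 3,000, 22% mortality and equal level sizes, a log-linear gradient (relative risk 0.80 across the range) gives 55% power for a trend test, 23-45% for a split and 31% for nominal levels. A step of relative risk 0.80 after the third level gives 81%, 90% (matching split) and 68%.

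**Conclusion.** The concern holds. By v5.0's own account, the titre analysis was changed in the light of the outcome data, the thresholds are left open, and inference is unadjusted. Titre p-values and intervals from such splits do not have their nominal error rate.

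The size is uncertain. Every combined strategy examined exceeded 5%, from about 8-9% with one outcome-blind cut to 20-23% with the best of six. The upper figure is the full-search case, not a measured rate. All the figures rest on assumed titre distributions and an assumed spline form. That the inflation exists follows from the text; how large it is cannot be fixed from the documents.

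**What to change.** - Report the spline partial-likelihood test planned in SAP v2.0, with the covariate adjustment that v5.0 calls for, as the titre result whatever its p-value.
- Label every low/high or low/medium/high result post hoc and exploratory at the place where it is reported, not only in the SAP.
- State each threshold examined and its assay basis.
- Show all six splits, or a p-value adjusted for a maximally selected cut (roughly nominal p < 0.01 for six cuts), in place of an unadjusted test of one chosen split.
- Use one titre grouping in both Primary and Secondary Data Analysis.

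A 1-df trend on log2 titre may be added as a supplement. It is not part of the required fix: it was not in the plan, would itself be chosen after the data were seen, and makes the linear assumption that the spline was meant to avoid.

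The cost is SAP wording and a few model fits on existing data. The downside is that a favourable split may lose its claim to significance.

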### Secondary Data Analysis: In the future, additional secondary data analyses to assess for risk modification can follow in two ways. First variable by concentration interactions terms can be added to the Cox model. While this approach is statistically efficient, the complexity of the resulting model will make real-world interpretations of the findings challenging. To address this, a Breslow-Day stratified analysis approach will be considered. For this initial report, separate results by strata of interest are presented. The strata presented represent important subsets of the data that warrant further consideration.

For this future analysis, estimated mortality rates will be estimated using the product limit estimator for each stratum of the data. This approach will follow a generally hierarchical process. First, as noted above, the data will be stratified by time of transfusion, infusion volume, and antibody concentration level. Next, stratification will be based on admission to ICU at time of transfusion, yes or no, which result in multiple strata of interest (e.g., ICU patients transfused within 3 days using 2 units of plasma with high concentration of neutralizing antibodies). This general approach will continue with additional risk modifiers as indicated below to result in finer and finer sub categorization of patients. These estimates will be visualized with forest plots to provide an overall impression of heterogeneity among the risk modifiers. As with the primary analysis, the data will be grouped so that the three antibody concentrations levels will be collocated on the figure to provide some evidence of the dose-response relationship, if one exists. Formal tests for the effect modification will be conducted using the Cox framework using appropriately chosen interaction terms.

**Risk Modifiers**

1. Calendar month of Covid-19 convalescent plasma transfusion
2. Age
3. Gender/Sex
4. Race
5. Ethnicity
6. BMI
7. ICU at time of Covid-19 convalescent plasma transfusion
8. Level of respiratory support at time of Covid-19 convalescent plasma transfusion
9. Body Composition: Height, Weight, BMI
10. No. of days from Covid-19 symptom onset to convalescent plasma transfusion
11. COVID-19 Severity
12. At risk of severe / life threatening COVID-19
13. Currently has severe / life threatening COVID-19 with further delineation of why (Y/N to each of the following: dyspnea, respiratory rate >=30/min, spo2 <= 93%, p/f <300, lung infiltrates > 50 within 24 – 48 hrs, respiratory failure, septic shock, multi-organ dysfunction or failure)

**Study Protocol Amendments Summary**

| **Version** | **Description of Change** |
| --- | --- |
| **1.0** | Not applicable. |
| **2.0** | The initial statistical vignette was developed into a robust statistical analysis plan with consideration of putative risk factors identified in contemporary Covid-19 clinical trials. |
| **3.0** | Additional details regarding the performance characteristics of a semiquantitative, pseudo neutralizing antibody assay revealed a range of six categorical dilution coefficients (1:80, 1:160, 1:320, 1:640, 1:1280, 1:2560), that informed the stratification of anti-SARS-CoV-2 antibody level as “low”, “medium” and “high”. |
| **4.0** | An additional component of the analysis, considering the effects of timeliness of transfusion and categorical antibody level was added. Six stratifications (3×2) were planned, using a dichotomous split for timeliness (with 3 days vs. 4 or more days) and three anti-SARS-CoV-2 antibody levels. |
| **5.0** | In an extension of the baseline Cox regression model fitted to the data, a combination of ‘conditional’ method for estimating survival and bootstrap methods were used to estimate the relative risk of mortality. |
| **6.0** | An exploratory analysis using a machine learning approach to link mortality with both anti-SARS-CoV-2 antibody levels and adjustment variables was developed during the drafting of a previous manuscript. |

1. Study Protocol Version 1.0 was a draft. Study Protocol Version 2.0 represents the initial protocol document approved by the Mayo Clinic Institutional Review Board (IRB) on April 4, 2020. [↑](#footnote-ref-1)
2. Study Protocol Amendment history is embedded in each Study Protocol Version, and has been duplicated in a separate section for clarity. [↑](#footnote-ref-2)
3. Statistical Analysis Plan 1.0 was a vignette describe in Section 8 of the Study Protocol. Statistical Analysis Plan 2.0 represents the initial descriptive analysis plan. [↑](#footnote-ref-3)
